## Abstract

**Background:**

Hypertension is a major public health issue due to its association with cardiovascular disease risk. Despite the availability of effective antihypertensive drugs, rates of blood pressure (BP) control remain suboptimal. Renal denervation (RDN) has emerged as an effective non-pharmacological, device-based treatment option for patients with hypertension. The multicenter, single-arm, observational Global Paradise™ System (GPS) registry has been designed to examine the long-term safety and effectiveness of ultrasound RDN (uRDN) with the Paradise System in a large population of patients with hypertension.

**Methods:**

The study aims to enroll up to 3000 patients undergoing uRDN in routine clinical practice. Patients will be recruited over a 4-year period and followed for 5 years (at 3, 6, and 12 months after the uRDN procedure and annually thereafter). Standardized home BP measurements will be taken every 3 months with automatic upload to the cloud. Office and ambulatory BP and adverse events will be collected as per routine clinical practice. Quality-of-Life questionnaires will be used to capture patient-reported outcomes.

**Conclusions:**

This observational registry will provide real-world information on the safety and effectiveness of uRDN in a large population of patients treated during routine clinical practice, and also allow for a better understanding of responses in prespecified subgroups. The focus on home BP in this registry is expected to improve completeness of long-term follow-up and provide unique insights into BP over time.

**Graphical abstract:**

Global Paradise System registry study design. ABP, ambulatory blood pressure; BP, blood pressure; FU, follow-up; M, month; OBP, office blood pressure.

[figure not shown]

## Introduction

Hypertension is highly prevalent [1, 2] and is the most common modifiable risk factor for cardiovascular disease [3]. A number of factors contribute to uncontrolled hypertension, including inappropriate treatment (doses and combinations) due to physician inertia and poor medication adherence [4, 5]. In addition, a subset of patients have hypertension that is truly resistant to optimal guideline-directed triple pharmacotherapy (in whom adherence has been confirmed) [6–9].

Renal denervation (RDN) has emerged as an effective non-pharmacological treatment option for patients with uncontrolled and resistant hypertension [10, 11]. Ultrasound RDN (uRDN) with the Paradise™ Ultrasound Renal Denervation system (Recor Medical, Palo Alto, CA, USA) has been shown to be safe and effective, resulting in significant and durable reductions in BP in the presence and absence of antihypertensive drugs [12–18].

As the number of patients treated with uRDN in clinical practice increases, the GPS Registry has been set up to document the real-world long-term safety and effectiveness of uRDN in patients treated in routine clinical practice.

## Methods

### Study design

The GPS Registry (NCT05027685) is a multicenter, single-arm, observational study (Fig. 1). Up to 200 study centers from areas where the Paradise System (Recor Medical, Palo Alto, USA) is available will enroll patients, including but not limited to the European Union, the United Kingdom, Switzerland and Monaco. Additional locations may be added to the GPS Registry over time. Monitoring of study sites will be performed during the registry to assess continued adherence to the protocol and applicable regulations. The recommended follow-up is 5 years.

**Fig. 1 Fig1:**
[figure not shown]
Paradise ultrasound renal denervation system

All national and local approvals will be obtained prior to beginning the study. Any additional requirements imposed by the institutional review board/ethics committee (IRB/EC) or regulatory authority will be followed where appropriate. Annual IRB/EC renewals will be obtained throughout the duration of the registry as per local/country requirements. Written informed consent will be obtained from all patients or their legally designated representative, as defined by local regulations, in accordance with the Declaration of Helsinki.

The GPS Registry will be run under the guidance of a Steering Committee that will include international physicians with expertise in the areas of RDN, vascular medicine, hypertension, cardiology, interventional cardiology, radiology, and nephrology.

### Study population

Based on the international guidelines that have been recently published, patients qualifying for renal denervation should have been unsuccessful in controlling their blood pressure with lifestyle changes and antihypertensive medications. Patients selected for uRDN with the Paradise System as per routine clinical practice on patient selection for renal denervation can be enrolled in the registry. The goal of the study is to collect real-world data on current clinical practices at each participating site. Full details of the study inclusion and exclusion criteria are shown in Table 1. For prospectively enrolled patients, the uRDN procedure is to be scheduled within 30 days of registry enrollment, while retrospectively enrolled patients need to have undergone uRDN within the previous 6 months.

**Table 1 Tab1:** Inclusion and exclusion criteria

Inclusion criteria
Age ≥ 18 years at time of consent
Candidate for uRDN with the Paradise System based on physician’s assessment
OR
Treated with uRDN using the Paradise System within the 6 months prior to consent
Willing to provide written informed consent (appropriately signed and dated) and agreed to have all study procedures performed

Exclusion criteria
Stented renal artery
Age < 18 years
Pregnancy
Known allergy to contrast medium not amenable to treatment
Renal arteries with diameter < 3 mm and > 8 mm^a^
Renal artery with fibromuscular disease^a^
Renal artery aneurysm or dissection^a^
Renal artery stenosis of any origin > 30%^a^
Iliac/femoral artery stenosis precluding insertion of the Paradise catheter^a^

^a^Determined at time of procedure

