### Assessments and data collection

Follow-up visits are scheduled at 3, 6, and 12 months after the uRDN procedure and every 12 months thereafter. Each visit will include medical review, measurement of office BP, medication name and dose). Ambulatory BP data (mean values, heart rate, standard deviation) obtained during routine clinical practice at study centers (including daytime, nighttime and 24-h BP) will be recorded and assigned to the nearest follow-up visit.

Other data collected during routine clinical practice will also be reviewed as part of patient follow-up, including any of the following: physical parameters including body weight, HR, seated and standing office BP; smoking status during follow-up, socioeconomic, and healthcare resource use parameters; electrocardiogram; non-invasive cardiac imaging; urinalysis including micro/macroalbuminuria; blood chemistry (serum creatinine, electrolytes, blood glucose and HbA1c, blood lipids); non-invasive renal artery imaging; any other cardiovascular procedures and treatments including glucose- and cholesterol-lowering drugs and antiplatelet/anticoagulant use, and the occurrence of any cardiovascular/cerebrovascular event (MI, HF, AF, etc.) and cardiovascular or non-cardiovascular death.

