### Sample size

The sample size for the Registry is based on the intent to characterize the safety and effectiveness data in a real-world patient population. The target is to enroll up to 3000 patients at up to 200 sites globally and follow them up to 5 years after enrollment. This sample size should provide a high degree of statistical precision on home and office blood pressure changes and a high probability of observing rare safety events; with a sample size of 3000 subjects, there is a 95% probability of observing events that occur at a population rate as low as 0.1%.

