### Statistical analysis

Every effort will be made to minimize the amount of missing data. Statistical analyses will be descriptive. Continuous variables will be summarized as mean ± standard deviations and median (range) with interquartile range. Categorical variables will be summarized as frequencies and percentages. Analysis of clinical effectiveness and safety (Table 2) data will be performed on the total study population and in clinically relevant participant subgroups (e.g., based on age, history of chronic kidney disease, heart failure, atrial fibrillation, sleep apnea, diabetes mellitus, etc.). An additional analysis will determine whether BP parameters can help predict patients that may be more likely to respond to uRDN. Subgroup analyses and multivariable analyses will be performed.

**Table 2 Tab2:** Standard of care parameters collected, effectiveness and safety assessments

Standard of care parameters
Demographics
Medical history
Office blood pressure
Medication usage
Short Form-12 quality-of-life questionnaire
Socioeconomic and healthcare resource use parameters
24-h ambulatory blood pressure monitoring
Electrocardiogram
Cardiac imaging
Urine chemistry
Blood chemistry
Renal artery imaging
Renal denervation procedure
Cardiovascular procedures and treatments

Effectiveness assessments
Reduction in average home systolic/diastolic BP in mmHg compared with enrollment
Reduction in average office systolic/diastolic BP in mmHg compared with enrollment
Reduction in average ambulatory systolic/diastolic BP in mmHg (daytime, nighttime and 24-h) compared with enrollment
Proportion of patients with home, office and ambulatory systolic BP reductions of ≥ 5 mmHg, ≥ 10 mmHg, and ≥ 15 mmHg post procedure
Proportion of patients meeting BP control criteria at follow-up (according to current guidelines)
Change in office/home/ambulatory pulse pressure in mmHg at follow-up compared with enrollment
Change in office/home/ambulatory heart rate in beats/min at follow-up compared with enrollment
Proportion of subjects without any antihypertensive treatment at follow-up, with analysis stratified by number of antihypertensive medications at enrollment
Analysis of quarterly home BP in mmHg at follow-up
Change in Short Form-12 quality-of-life scores during follow-up compared with enrollment

Safety assessments
All-cause mortality
Hospitalization for major cardiovascular- or hemodynamic-related events (e.g., heart failure, atrial fibrillation)

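### Patients enrolled up to 6 months after uRDN must have survived to consent, so pooling them from the procedure date understates early mortality and fatal complications

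*Protocol article*

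**What the plan says.** All references are to the protocol article.

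- **Entry.** The *Study population* section and Table 1 give two routes. Prospective patients have the procedure scheduled within 30 days of enrolment, "while retrospectively enrolled patients need to have undergone uRDN within the previous 6 months". Table 1 words the second route as "Treated with uRDN using the Paradise System within the 6 months prior to consent".
- **Consent.** Both routes share one condition: "Willing to provide written informed consent (appropriately signed and dated) and agreed to have all study procedures performed". *Study design* adds that "Written informed consent will be obtained from all patients or their legally designated representative, as defined by local regulations".
- **Time origin.** In *Assessments and data collection*, "Follow-up visits are scheduled at 3, 6, and 12 months after the uRDN procedure and every 12 months thereafter".
- **Analysis population.** In *Statistical analysis*, "Analysis of clinical effectiveness and safety (Table 2) data will be performed on the total study population", and also in clinical subgroups. The subgroups named are age and comorbidities; entry route is not among them. All-cause mortality heads the safety list in Table 2, with no time window attached.
- **Size.** *Sample size* justifies 3000 patients partly by "a high probability of observing rare safety events", put at 95% for an event with a population rate of 0.1%.

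**The concern.** A patient who enters after treatment was, by construction, alive on the consent date. The time from procedure to consent, up to 6 months, is immortal: no death can be recorded in it, because a patient who died then never joins the registry. If that patient is nevertheless counted from the procedure in the total population, the denominator holds people who could not have contributed an early death. The numerator lacks the deaths of people who would otherwise have been enrolled.

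The registry exists to document safety in routine use, and its *Discussion* names detection of rare events as a main reason for large registries. It is single-arm, so no comparator carries the same bias and offsets it. An early mortality figure from the pooled cohort would be read as the risk of the treatment and would be too low. The sample size statement is affected as well, since it treats all 3000 patients as observable for any event.

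**Working it through.** **The plan's own figure.** Probability of at least one event at rate 0.1% among 3000: 1 − (1 − 0.001)^3000 = 0.9503. The stated 95% is reproduced, provided all 3000 can be observed for the event.

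**Inputs.** From the article: a retrospective window of 6 months, follow-up timed from the procedure, pooled analysis, N = 3000. Assumed, because the article does not give them: retrospective share r of 10% to 50%, consent time U uniform over 0 to 6 months, constant and small hazard.

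**Mortality.** A retrospective patient can contribute a death within T months only after consent, so the expected share of the window at risk is E[max(0, T − U)]/T.

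- T = 1 month: (1/6) × ∫₀¹(1 − u)du = 1/12. Fraction of true mortality seen = 1 − (11/12)r.
- T = 6 months: (6 − 3)/6 = 1/2. Fraction seen = 1 − r/2.
- T = 12 and 60 months: mean lost time is 3 months. Fraction seen = 1 − (3/12)r and 1 − (3/60)r.

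| r | 1 month | 6 months | 1 year | 5 years |
|---|---|---|---|---|
| 10% | 91% | 95% | 97.5% | 99.5% |
| 20% | 82% | 90% | 95% | 99% |
| 30% | 73% | 85% | 92.5% | 98.5% |
| 50% | 54% | 75% | 87.5% | 97.5% |

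A calculation without the small-risk approximation agrees. With true 6-month mortality of 1.00% (assumed), the pooled figure is 0.95% at r = 10% and 0.75% at r = 50%. The matching one-month mortality of 0.167% reads 0.152% and 0.091%.

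**Probability of seeing a rare early fatal event.** Only prospective patients are fully observed from the procedure, so n = 3000(1 − r).

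- r = 10%: n = 2700, 1 − 0.999^2700 = 93.3%. The rate detectable with 95% probability is 1 − 0.05^(1/2700) = 0.11%.
- r = 50%: n = 1500, 1 − 0.999^1500 = 77.7%. The rate detectable with 95% probability is 0.20%.

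These hold for deaths at or close to the procedure. For deaths spread over the first month, retrospective patients add about 1/12 of their number: n = 2700 + 25 = 2725 gives 93.5%, and n = 1500 + 125 = 1625 gives 80.3%. The conclusion is the same.

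**Non-fatal events and BP.** Here the result depends on whether patients with the outcome are more or less likely to be enrolled (relative probability w), which the article does not tell us. Take r = 50%.

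- Non-fatal event, true rate p = 1.0% (assumed): the retrospective rate is pw/(pw + 1 − p). The pooled rate is 1.00% at w = 1, 0.90% at w = 0.8, 0.75% at w = 0.5 and 1.12% at w = 1.25.
- BP change, assumed normal with mean −10 and SD 15 mmHg, w applying to below-average responders: the retrospective mean is −10 − 15√(2/π)(1 − w)/(1 + w). The pooled mean is −10.0 at w = 1, −10.7 at w = 0.8, −12.0 at w = 0.5 and −9.3 at w = 1.25.

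The sign changes with w.

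**The case against.** **Long-term aim.** The registry's aim is long-term and Table 2 gives mortality no window; at 5 years the loss is 0.5% to 2.5% (relative). This stands, and it confines the point to early mortality. The share r is also unknown, so the size is conditional. The direction is not.

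**Condensed article.** Handling by entry route may be in the full protocol or SAP, the subgroup list is open-ended, and the analyses are descriptive. The first two are fair. But the point rests on what is stated: the entry rule, the time origin and the pooled population. A by-route table elsewhere would not repair the total-population mortality figure, and a descriptive rate can be biased.

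**Consent by a representative.** The clause in *Study design* does not clearly reach patients already dead, and Table 1 still requires agreement to study procedures.

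**The stronger reading.** A reader might infer that procedural safety as a whole and the BP response also look better than they are. The article does not support this:

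- Most of the procedural events listed in Table 2 can be survived. Such patients can consent and have the event recorded.
- Sites know the early course when they approach patients, but those with complications or a poor response may be seen more often and approached more readily.
- Under *Home blood pressure*, retrospective patients get no study device, so follow-up telemetric home BP, the registry's focus, comes only from prospective patients.
- Table 2 measures BP change from enrolment. Read literally, that is after the procedure for retrospective patients and would shrink their apparent reduction.

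**Conclusion.** The point holds for early all-cause mortality and fatal peri-procedural complications. Followed as written, the plan understates both whenever any patient is enrolled after treatment. With a retrospective share of 10% to 50%, uniform consent times and a constant hazard, the relative understatement is about 9% to 46% at one month and 5% to 25% at 6 months, and it is minor by 5 years. The 95% probability in *Sample size* is correct arithmetic but does not apply to early fatal events, where about 93% to 78% is realistic over the same range of shares. For non-fatal procedural events and office or ambulatory BP, enrolment after the outcome is known is a possible source of bias of undetermined direction; no claim that these look too favourable can be made from the article.

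**What to change.** In *Statistical analysis*, state that:

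1. 30-day and 6-month mortality and fatal complications are headlined on prospectively enrolled patients, with retrospective patients shown separately.
2. Mortality over time in the full cohort is measured from the procedure, with retrospective patients entering the risk set at their consent date (delayed entry).
3. Non-fatal procedural events and BP response are reported by entry route. Events recorded in retrospective patients are kept; delayed entry should not be used to discard them.

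In *Sample size*, restate the probability of observing a rare event for early fatal events, using the number of prospective patients expected.

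The change is to analysis and reporting. Consent is already dated and visits are already timed from the procedure, so enrolment, treatment and total size are unaffected. The cost is a smaller denominator and less precision for early fatal events. Delayed entry removes the immortal time but not selection on a known outcome, which is why the by-route reporting in item 3 is needed as well.

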### Renal denervation procedure

The Recor Paradise System is a catheter-based system that delivers ultrasound energy to thermally ablate and disrupt the renal efferent and afferent sympathetic nerves, with the goal of achieving a reduction in systemic arterial BP and mitigating end-organ effects due to sympathetic over-activity. The system includes a single-use 6F catheter and an automated, portable, customized generator. The Paradise Catheter is intended to be employed in a catheterization laboratory under fluoroscopic guidance via femoral access only. The catheter consists of a through-lumen shaft with a cylindrical piezoelectric ceramic transducer located at the distal end of the catheter. The catheter has a distal balloon, which is pressurized by the generator to 1.5–2.0 atm using sterile circulating water.

The device's ultrasound transducer converts electrical energy into acoustic energy, which is then delivered radially through the cooling balloon into the renal artery. The pressurized balloon centers the ultrasound transducer within the artery, and the circulation of fluid serves as coolant to protect the endothelial and medial layers of the renal arterial wall. Each catheter has an embedded chip that communicates directly with the generator and specifies the power settings to be applied.

The uRDN procedure will be performed according to routine practice at each study site and consistent with the device’s instructions for use. As treatment is bilateral, specific angiographic requirements need to be met to deem anatomic eligibility. Measurements of the distal, mid, and proximal renal artery diameters are used to select the appropriate Paradise catheter balloon size. The treatment strategy requires operators to deliver a minimum of two (to three) sonications in each main renal artery and the first sonication should be delivered at a distance of at least 5 mm from the artery bifurcation. The Instructions for Use includes details for balloon sizing and treatment strategy regarding the number of emissions per artery and also includes instructions for additional sonications in case there are proximal bifurcations or accessory arteries. Physicians new to the technology will receive proctoring support for initial cases as needed.

Procedural support by a sponsor representative is available to all sites regardless of experience with the Paradise Renal Denervation System.

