Hypertensive crisis or symptomatic hypotension
New-onset stroke, transient ischemic attack, cerebrovascular accident
Acute myocardial infraction
Any coronary revascularization
Major vascular complication (e.g., clinically significant groin hematoma, arteriovenous fistula, pseudoaneurysm) requiring surgical repair, interventional procedure, thrombin injection, or blood transfusion)
New renal artery stenosis > 70% confirmed by CTA/MRA
Renal artery perforation or dissection requiring an invasive intervention
New-onset (acute) end-stage renal disease (eGFR < 15 mL/min/m^2^ or need for renal replacement therapy)
Significant decline in renal function, defined as a ≥ 50% increase in serum creatinine (mg/mL)

BP, blood pressure; CTA, computed tomography angiography; eGFR, estimated glomerular filtration rate; MRA, magnetic resonance angiography

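### The stent exclusion in Table 1 has no time point, so it can be read to keep out retrospective patients stented because of the uRDN procedure

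*Protocol article*

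**What the plan says.** All references are to the protocol article.

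- **Entry routes (Study population and Table 1).** A patient may enter before treatment as a candidate for uRDN, or afterwards: "Treated with uRDN using the Paradise System within the 6 months prior to consent". The text of the section repeats the window: "retrospectively enrolled patients need to have undergone uRDN within the previous 6 months".
- **Exclusions (Table 1).** There is one list for both routes, and the section presents the table as the full criteria. Four renal artery items (diameter, fibromuscular disease, aneurysm or dissection, stenosis above 30%) and the iliac/femoral item carry footnote a: "Determined at time of procedure". The item "Stented renal artery" carries no footnote and no other time reference.
- **Safety outcomes (Table 2, Safety assessments).** These include "Renal artery perforation or dissection requiring an invasive intervention" and "New renal artery stenosis > 70% confirmed by CTA/MRA". The Safety section names the same kinds of event.
- **Sample size.** The target is up to 3000 patients. The article says this gives a 95% probability of observing an event with a population rate of 0.1%.

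**The concern.** For a patient enrolled before treatment, a renal stent found at screening can only be an old one. For a patient enrolled afterwards, it may be the result of the procedure under study. The criterion does not separate the two cases. A site that checks it at consent, as it would check age, could turn away a patient whose artery was stented because uRDN had dissected or perforated it, or because a stenosis had developed since.

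That would be selection on the outcome. The patient would be missing from the numerator and from the 5-year follow-up, and the error runs in one direction only. The article justifies the registry's size by its ability to detect rare safety events. At a rate of 0.1%, 3000 patients are expected to yield 3 events, so losing even one would matter.

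**Working it through.** **Reading the criteria side by side**

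1. *Stent criterion.* No footnote and no mention of procedure or consent. For a retrospective patient the text fits either the state before uRDN or the state at consent, up to 6 months later. On the second reading, a stent placed after uRDN excludes.
2. *Dissection and stenosis criteria.* For example, "Renal artery aneurysm or dissection" carries footnote a. A lesion that first appears between the procedure and consent is therefore not barred.
3. *Prospective patients.* They enrol before uRDN, so the stent criterion cannot pick up a consequence of the procedure.
4. *Events not stented.* Perforation is not itself an exclusion, and an injury managed by another invasive intervention, or a new stenosis without a stent, does not meet the stent criterion.

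The exposure is therefore limited to retrospective patients whose renal artery was stented between uRDN and consent.

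**Upper bound on the effect**

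Inputs: N = 3000 and p = 0.001 (Sample size section). The retrospective share f is not stated, so 20%, 30% and 40% are assumed.

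The plan's own figure first: P(at least one event) = 1 − (1 − p)^N = 1 − 0.999^3000 = 0.950. The stated 95% reproduces.

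Now suppose that every such event in a retrospective patient is barred. Only 3000 × (1 − f) patients can contribute one, while the denominator stays at 3000:

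| Assumed f | Patients who can contribute | P(at least one event) | Expected crude rate |
|---|---|---|---|
| 0% | 3000 | 1 − 0.999^3000 = 95.0% | 0.100% |
| 20% | 2400 | 1 − 0.999^2400 = 90.9% | 0.080% |
| 30% | 2100 | 1 − 0.999^2100 = 87.8% | 0.070% |
| 40% | 1800 | 1 − 0.999^1800 = 83.5% | 0.060% |

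The crude rate is 0.1% × (1 − f), so the relative understatement equals f. The bound is reached only if every site reads the criterion literally and every event in retrospective patients was stented before consent.

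**The case against.** The strongest reply is that the missing footnote has an ordinary explanation. An old stent, like age, pregnancy or contrast allergy, can be known from history, whereas the footnoted items need the procedural angiogram. On that view the stent criterion describes the artery before treatment. No section says that stenting after uRDN excludes anyone, and assessment at consent is an inference. This stands as far as intent goes: the text permits the exclusion but does not show that it is meant or has happened. It does not remove the ambiguity, because one list covers both routes and this item has no time point.

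A reader might also infer that the dissection and stenosis exclusions remove injuries caused by the catheter. The document does not support that. Footnote a limits those items to the procedure, and they stand beside plain candidacy conditions such as artery diameter and iliac/femoral access. The Renal denervation procedure section says that "specific angiographic requirements need to be met to deem anatomic eligibility", immediately before it describes choosing the balloon size, so this reads as screening before treatment. What remains is a small gap: the footnote does not say in so many words that the assessment precedes catheter introduction or energy delivery.

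Two further points are fair. Device-related adverse events also go to the regulatory authorities through vigilance reporting, but that does not restore the patient to the registry's numerator or follow-up. Stenosis that develops later can still be captured during follow-up, so the bound is especially loose for that outcome. The fact that this is a condensed article carries less weight, because the article presents Table 1 as giving the criteria in full.

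**Conclusion.** The point holds for the stent criterion alone. Applied literally to a patient who consents after uRDN, it can exclude someone stented for a complication that the registry sets out to count, and any resulting bias lowers the reported renal artery safety rates.

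The actual size is unknown. It depends on the retrospective share, on how sites read the item, and on how many events were stented before consent, none of which the article gives. The tabulated figures are worst-case bounds under assumed shares, not estimates. They apply only to the renal artery injury and stenosis outcomes; the 95% statement is arithmetically correct and is untouched for outcomes such as death, stroke or myocardial infarction.

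It would go too far to say that these patients are excluded, or that the rates are too low by construction.

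**What to change.** Add a sentence to Table 1 or its footnotes: for retrospectively enrolled patients, the stent criterion, and for clarity the renal artery criteria under footnote a, refer to the state before the index uRDN procedure. Renal artery injury, stenosis or stenting during or after that procedure is a safety outcome and not a reason for exclusion from the registry.

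Optionally, ask sites whether any retrospective candidate has been screened out on this ground, since patients never enrolled cannot be recovered at analysis.

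The cost is one line of text and, if chosen, a short site query. The change concerns eligibility for data collection only and adds no procedures.
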